**Table 3 Tab3:**
[figure not shown]
SPIRIT figure: schedule of enrolment, interventions, and assessments

Plans to promote participant retention and complete follow-up include email or text message reminders about appointments, participant empowerment, and resource facilitation.

#### Sample size

To detect a cognitive improvement, measured by the MMSE as a difference greater than 3 points at discharge between groups (bilateral α = 0.05, power = 0.90), 45 patients should be enrolled in each group. Assuming 15% losses, the final goal of each group is 53 patients, and consequently, a total sample size of 212 subjects.

#### Randomization and blinding

All patients hospitalized in the AGU will be screened for the eligibility criteria. The ones who meet the eligibility criteria will be randomly assigned to one of the IG or to the CG within the first 48 h of admission, following a simple randomization procedure in a 1:1:1:1 ratio without restriction. Randomization will be performed using the randomizer software (https://randomizer.org/) with a random permuted block design with block sizes.

Participants will be explicitly informed and reminded not to discuss their randomization assignment with the assessment staff. The assessment staff will be blinded to the participants’ group and the main study design. It is not possible to mask the group assignment to the staff involved in the IG training. Patients and caregivers/legal guardians (in case the patient has cognitive impairment) will be informed of their random inclusion in one group but will not be informed on the group in which they are. Figure 3.

**Fig. 3 Fig3:**
[figure not shown]
Flow diagram

#### Statistics

Initially, a descriptive analysis will be carried out in the total sample and in the groups. As for continuous variables, the statistics of central tendency and dispersion will be calculated according to the variable distribution (mean and standard deviation or median and interquartile range), whereas frequencies and percentages will be considered for qualitative variables, with respective confidence intervals in the overall prevalence. The baseline variables will be compared between the treatment and control groups using the Student’s t-test or Mann–Whitney U test for quantitative variables, and the Chi-square test or Fisher’s test for qualitative variables. The effect of the intervention on the different outcome variables will be analysed using ANCOVA models or linear mixed models for quantitative variables; logistic models, differences in rates or differences in proportions will be also performed for falls, mortality, and institutionalization. If any independent variable presented relevant baseline differences, a sensitivity analysis will be performed, adjusting for these variables. No missing data imputations are planned. The analysis follows the intention-to-treat principle, but per-protocol analysis will also be performed as a sensitivity analysis. To determine statistical significance, a level of 0.05 will be established. The data will be analysed with SPSS 25.0 and R software v.4.0.

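### Covariates for the adjusted sensitivity analysis are picked by chance baseline imbalance, after two-sample tests that do not fit four arms, rather than fixed in advance by prognostic value

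*Protocol article*

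**What the plan says.** Three statements in the protocol article bear on this.

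- **Randomization and blinding.** Patients are allocated "following a simple randomization procedure in a 1:1:1:1 ratio without restriction". The arms are control, IVR, ME and IVR + ME.
- **Statistics, baseline comparison.** "The baseline variables will be compared between the treatment and control groups", by Student's t or Mann–Whitney for quantitative variables and by chi-square or Fisher for qualitative ones.
- **Statistics, adjustment.** Quantitative outcomes are analysed by ANCOVA or linear mixed models. Then: "If any independent variable presented relevant baseline differences, a sensitivity analysis will be performed, adjusting for these variables".

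The significance level given is 0.05. No separate level is set for the baseline tests, and no threshold is set for a relevant difference.

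**The concern.** There are three problems, all in what the text states.

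1. **The tests are uninformative.** With random allocation, the hypothesis that the arms come from the same population at baseline is true by design. A small p-value shows only that an unusual draw occurred. It does not say whether the imbalance matters for the outcome.
2. **The tests do not fit the design.** Student's t and Mann–Whitney take two groups. With four arms, the wording means either three comparisons with control per variable or one comparison with three different interventions pooled. The article does not say which, and the two readings flag variables at different rates.
3. **The selection criterion is the wrong one.** A covariate earns its place by predicting the outcome. Under this rule a weak predictor that happens to be imbalanced is adjusted for, and a strong one that happens to be balanced is not. The list could also differ between contrasts and could not be known in advance.

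What is at stake is the value of the sensitivity analysis. A robustness check whose content is settled after looking at the data is a weak check, and it leaves room for selective emphasis when results are reported.

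**Working it through.** **Step 1. Numbers per arm (Sample size section).** The plan states 45 evaluable patients per group, 15% losses, 53 enrolled per group and 212 in total. Check: 45 / (1 − 0.15) = 52.9, rounded up to 53; 4 × 53 = 212. The plan's figures reproduce.

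**Step 2. How often chance flags one variable.** Assumption: relevant means p<0.05, the only level the article gives.

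- One contrast, or the three intervention arms pooled against control: 0.05 by definition.
- Three contrasts against a shared control: 200,000 simulated trials with 53 per arm, a normally distributed variable, no true difference, and t-tests on 2 × 53 − 2 = 104 degrees of freedom. At least one p<0.05 occurred in 0.125 of trials. As a check, three independent tests would give 1 − 0.95³ = 0.143. The shared control makes the tests positively correlated, so a somewhat lower figure is expected.

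The unresolved wording alone therefore moves the chance flag rate per variable between 5% and about 12.5%.

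**Step 3. What that means for a list of variables.** The number of baseline variables is not in the text available (the schedule table is not shown), so 10 and 15 are assumptions. The expected number flagged is k × rate and needs no independence. The chance of at least one flag is 1 − (1 − rate)^k and does assume independence.

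| k | Expected flags, pooled (5%) | Expected flags, three contrasts (12.5%) | At least one, pooled | At least one, three contrasts |
|---|---|---|---|---|
| 10 | 0.5 | 1.2 | 40% | 74% |
| 15 | 0.75 | 1.9 | 54% | 86% |

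MMSE, TMT-A, Barthel, HABAM and handgrip are likely to be correlated, so the last two columns probably overstate the risk.

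**Step 4. Does the rule damage error rates?** As a worst case that the article does not plan, suppose the rule governed the main result. In 40,000 simulated two-arm comparisons (45 per arm, one covariate, adjusted for only if its baseline p<0.05), type I error was 0.048, 0.041 and 0.035 for covariate–outcome correlations of 0.3, 0.5 and 0.7. The nominal level is 0.05, so the test becomes conservative and is not inflated.

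**Step 5. What prespecification buys.** Adjusting for a covariate with correlation r to the outcome multiplies the residual variance by 1 − r², whether or not the covariate is imbalanced. Once the baseline value of the outcome is in the model, r must be read as the partial correlation given that value. The article gives no such correlation, so the gain cannot be put in figures.

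**The case against.** The strongest defence is that the sentence on imbalance labels the adjusted analysis a sensitivity analysis. That ranks the two analyses in advance. This stands, and it rules out several stronger readings.

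- **A reader might infer that imbalance chooses the covariates of the primary model, or that two results compete unranked.** The text supports neither. The ANCOVA or mixed model is stated separately and comes first.
- **A reader might infer that p-values decide the adjustment.** The article says relevant, not significant, and does not tie the word to the tests. They are the only formal baseline comparison described, so the link is natural, but it is an inference, and the rates in Steps 2 and 3 depend on it.
- **A reader might infer that the primary model omits prognostic covariates.** ANCOVA ordinarily carries the baseline value of the outcome, and a fuller covariate list may be in a protocol or SAP not shown. Its absence from a journal article is not a fault.
- **A reader might infer a quantified loss of power.** With one covariate at r = 0.5 against none, power at 45 per arm would rise from 0.90 to 0.96. That uses an SD of about 4.3 to 4.4, back-solved because the article states none, and an assumed correlation. It also ignores the baseline value that ANCOVA would normally already include. It does not measure a loss under this plan.

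What the defence does not remove is the rule itself. The two-sample tests and the imbalance trigger are stated methods, not details left open. An SAP with a covariate list would have to replace this sentence, not add to it. The chi-square and Fisher tests can handle four groups, so the misfit is confined to the quantitative tests and to the two-group wording.

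**Conclusion.** The point holds in a limited form. The planned baseline tests are uninformative under randomisation, the quantitative ones do not match a four-arm design, and the covariates of the sensitivity analysis are selected by undefined, observed imbalance instead of prognostic strength. The main analysis is not determined by this rule, no stated figure changes, and no inflation of type I error is shown.

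The size that can be given is the chance flag rate per variable: about 12.5% over three contrasts with control, or 5% for a single or pooled contrast. Both assume that relevant means p<0.05. This is a minor to moderate weakness, worth correcting because the correction is nearly free.

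**What to change.** 1. Delete the baseline significance tests. Present baseline characteristics for each of the four arms without p-values.
2. Delete the imbalance trigger.
3. For each quantitative outcome, prespecify a model with the baseline value of that outcome (where it has one) plus a short list of prognostic covariates already collected. Age and admission Barthel Index are candidates, since eligibility requires both. The Global Deterioration Scale stage is another, if it is recorded for every patient; eligibility only requires ruling out stage 7. The investigators should settle the list on prognostic grounds before the data are seen.
4. Make the analysis adjusted only for the baseline value the sensitivity analysis.

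If a full protocol or SAP already fixes a covariate list, the sentence on imbalance should be replaced by that list.

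**Cost.** A wording change. Age and Barthel need no new data. With 4 × 45 = 180 evaluable patients, a model with four arm means and the baseline value leaves 180 − 5 = 175 residual degrees of freedom. Three further linear terms leave 172. The sample size is unchanged.

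### With 15% losses expected and no imputation planned, an ANCOVA of discharge scores would leave out about 32 of 212 randomised patients, and no named sensitivity analysis tests whether that matters

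*Protocol article*

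**What the plan says.** The Statistics section fixes three things that bear on missing outcomes.

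- Imputation and population: "No missing data imputations are planned. The analysis follows the intention-to-treat principle".
- Sensitivity analyses: per-protocol, and adjustment for variables that differ relevantly at baseline. No other is named.
- Model: outcomes "will be analysed using ANCOVA models or linear mixed models for quantitative variables". No rule says which model applies to which outcome.

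The Sample size section sizes the trial on an effect "measured by the MMSE as a difference greater than 3 points at discharge between groups", gives the requirement as "45 patients should be enrolled in each group", and continues: "Assuming 15% losses, the final goal of each group is 53 patients, and consequently, a total sample size of 212 subjects". It does not say what counts as a loss or why losses would occur.

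The abstract places the primary outcomes at discharge. They are MMSE, handgrip strength and HABAM, and the primary outcomes section describes HABAM as a daily assessment of function.

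**The concern.** A discharge-score ANCOVA can use only patients who have a discharge score. With nothing imputed, a result labelled intention-to-treat then rests on completers, and the sponsor's own planning figure puts the excluded share at 15%.

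The losses need not be harmless. Participants are acutely ill, aged 75 or older and severely dependent, and MMSE and handgrip both need a patient who can respond and make an effort. The article itself foresees delirium and death, since it measures the first and plans an analysis of the second. If patients who cannot be tested at discharge are also those doing worst, and this happens more in one arm, the treatment difference shifts.

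The planned sensitivity analyses would not show it. Baseline adjustment uses the same observed outcomes, and per-protocol narrows the sample further. This is a stated rule in the article, not a detail left for a separate analysis plan.

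**Working it through.** **1. The plan's own figure.** Inputs from Sample size: 45 per group, 15% losses, four groups.

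- 45 / (1 − 0.15) = 52.9, rounded up to 53; 4 × 53 = 212. Reproduced.
- Expected discharge scores: 53 × 0.85 = 45.05 per group and 212 × 0.85 = 180.2 in total.
- Patients outside a discharge-score ANCOVA: 0.15 × 212 = 31.8, about 32.

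The inflation restores 45 per group, so power is not the issue.

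**2. A working SD.** The article gives none. Solving the two-sample formula for a 3-point difference, two-sided 0.05, power 0.90 and 45 per group gives 4.39 (normal) or 4.34 (t-test). I assume 4.35.

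**3. Bias in an unadjusted comparison of completers.** Let m be the loss rate in an arm and D the number of points by which lost patients fall below completers. The completer mean exceeds the full mean by m × D, so

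bias (arm T minus arm C) = m_T × D_T − m_C × D_C.

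All rates and deficits below are assumptions, except the overall 15%:

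| Loss, C v T | Deficit, C v T | Unadjusted bias (MMSE points) |
|---|---|---|
| 15% v 15% | 3 v 3 | 0.45 − 0.45 = 0 |
| 15% v 15% | 3 v 6 | 0.90 − 0.45 = 0.45 |
| 10% v 20% | 3 v 3 | 0.60 − 0.30 = 0.30 |
| 10% v 20% | 5 v 5 | 1.00 − 0.50 = 0.50 |
| 5% v 25% | 5 v 5 | 1.25 − 0.25 = 1.00 |

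**4. Bias in the ANCOVA that the plan names.** Baseline adjustment removes part of this.

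- If loss follows only the baseline score, simulation gives a bias of about 0.
- If loss follows the unseen discharge score, completers are also better at baseline, by r times their advantage at discharge (equal SDs, baseline–discharge correlation r). Adjustment subtracts about r × r of the shift, leaving roughly unadjusted bias × (1 − r²).

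For 10% v 20% and a 3-point deficit:

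| r | 0.30 × (1 − r²) | Simulation (SD 4.35) |
|---|---|---|
| 0.6 | 0.30 × 0.64 = 0.19 | 0.21 |
| 0.7 | 0.30 × 0.51 = 0.15 | 0.15 |
| 0.8 | 0.30 × 0.36 = 0.11 | 0.12 |
| 0.9 | 0.30 × 0.19 = 0.06 | 0.06 |

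Against the 3-point target, 0.06 / 3 = 2% and 0.2 / 3 = 7%. For 5% v 25% and a 5-point deficit, the same rule gives 1.00 × 0.64 = 0.64 at r = 0.6 and 1.00 × 0.19 = 0.19 at r = 0.9.

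**5. Would the mixed-model option cure it?** For MMSE at baseline and discharge only, hardly. In 150 simulated trials (SD 4.35, r = 0.8, loss depending on the discharge score) the mixed-model and ANCOVA estimates correlated 0.996 and their averages agreed to within 0.01 point. HABAM is different: with daily scores, a mixed model keeps a patient who lacks only the last value.

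**The case against.** The strongest reply is that no imputation and intention-to-treat are compatible. A likelihood-based mixed model keeps patients with partial data under a missing-at-random assumption, and the article names such a model. That stands. A reader might infer that the plan contradicts itself, or that it forbids imputation; the text says only that none is planned, and the completer problem attaches to the ANCOVA option.

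A reader might also infer a bias of 10% or more of the 3-point target. Even at the mildest case of 10% v 20% and 3 points, 0.3 / 3 = 10% belongs to an unadjusted comparison of means, which is not a named model. Baseline adjustment cuts it to about 2–7%.

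Nor do the documents show that loss comes from deterioration or differs by arm. The article gives one loss figure for all groups and mentions voluntary withdrawal. It excludes delirium, instability and end-stage disease at entry, blinds the assessors, and says patients are not told their group. Some losses could be among fitter patients, which would reverse the sign. Against this, only the intervention arms add headset or exercise sessions, which are evident to those receiving them, so unequal loss is plausible but not established.

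Finally, details of imputation models commonly sit in an analysis plan. That is fair for the details, but the article has fixed the rule and listed its sensitivity analyses, and none addresses missing outcomes.

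**Conclusion.** The point holds in limited form, as a cheap improvement. Under the ANCOVA option, about 32 of 212 randomised patients are expected to leave the primary analysis, if the 15% losses are patients without a discharge score. Nothing in the plan tests the effect of that.

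Whether bias follows is unknown. It requires that loss depend on the unobserved discharge state and that the loss process differ between arms, in rate or in how ill the lost patients are. With assumed losses of 10% v 20%, a 3-point deficit, SD 4.35 and baseline correlations of 0.6 to 0.9, the bias in adjusted ANCOVA is about 0.06 to 0.2 MMSE points. It would favour the arm with more losses. Larger deficits or more unequal losses raise it; equal loss with equal deficit gives none, and loss driven by baseline gives about none after adjustment. These figures do not show that the result would be wrong, only that the plan cannot show it is robust.

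**What to change.** - **Primary model.** Name one model per primary outcome and state that it assumes outcomes missing at random given baseline. For MMSE, baseline-adjusted ANCOVA or a two-visit mixed model will give nearly the same answer, so the choice matters less than fixing it in advance. For HABAM, use a mixed model on the daily scores, so that patients lacking only the discharge value stay in.
- **Sensitivity to missing outcomes.** Replace "No missing data imputations are planned" with a sensitivity analysis of each primary outcome: multiple imputation from data already collected, with a delta shift applied by arm and increased until the conclusion changes. Daily HABAM is documented as a predictor. The timing of Barthel, CAM and CIRS-G is in the schedule table, whose content is not visible here, so check it before relying on them.
- **Deaths and untestable patients.** Add one analysis that ranks them worst.
- **Reporting.** Give the number and reasons for missing discharge outcomes by arm.

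The cost is a revised paragraph and some extra analysis, with no change to the sample size. The downside is a possibly less favourable sensitivity result.

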### Description of interventions and usual care

Patients will be randomly assigned to the following described control group (CG) or to any of the following intervention groups (IG). Participants or their relatives will be able to discontinue the study for any reason at any time. Geriatricians of the AGU will offer physiotherapy whenever considered necessary, regardless the group assignment of patients, since restoring functional movements and reducing the physical decline during hospitalization is part of the usual care of AGU of HUN. Figure 1.

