#### Primary outcome measures

Mini-Mental State Examination (MMSE) [39] (a 30-point questionnaire; scale of 0 [worst] to 30 [best]).Isometric handgrip strength: the dominant-hand strength will be measured using a hand dynamometer (Takei Scientific Instruments Co., Tokyo, Japan). Patients will sit down with the elbow on complete extension and 5–10º of abduction. From this position, they will be asked to squeeze the handle as forcefully as possible for 3” twice. The highest result will be considered for data collection.Hierarchical Assessment of Balance and Mobility (HABAM) scale. The daily functional status will be assessed with the HABAM, an instrument that provides a clinical assessment of in-bed mobility, transfers, and ambulation [40]. A value of 0 is equal to the lowest or inability of performance. Changes in performances can be recorded with patient progress.

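### Three primary outcomes in four arms share one 0.05 level with no primary contrast or success rule, and the 0.90 power is supported only for a single unadjusted MMSE comparison

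*Protocol article*

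**What the plan says.** All places are in the protocol article.

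- **Primary outcome measures** lists three: MMSE, handgrip ("Isometric handgrip strength: the dominant-hand strength will be measured using a hand dynamometer") and HABAM. The Methods paragraph of the **Abstract** instead puts isometric strength with mood, quality of life and acceptance of IVR, as a further measure.
- **Introduction** (last paragraph) and **Description of interventions and usual care** give four parallel arms at 1:1:1:1: IVR, ME, IVR + ME and control. The aim covers both cognitive and functional domains against usual care.
- **Sample size** uses MMSE alone: "measured by the MMSE as a difference greater than 3 points at discharge between groups", with "bilateral α = 0.05, power = 0.90", from which "45 patients should be enrolled in each group". It does not say which groups are compared and gives no SD. Losses are then added: "Assuming 15% losses, the final goal of each group is 53 patients".
- **Statistics** names ANCOVA or linear mixed models for quantitative outcomes and closes with "To determine statistical significance, a level of 0.05 will be established".

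The article names no primary contrast and no order among the outcomes. It does not split the level, and it does not say whether one or all primary outcomes must be significant.

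**The concern.** Three outcomes and three comparisons with control make nine candidate primary tests; with all pairs of arms there are 18. Under a single undivided 0.05 and no success rule, a p-value just under 0.05 for handgrip in one arm could be reported as a positive primary result. That result would carry a much higher false positive risk than 5%.

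The sample size is a decision this article does make, and it leaves no room for a correction. If multiplicity is controlled later, the stated 0.90 no longer describes the test that will be run, unless baseline adjustment makes up the loss. Handgrip and HABAM have no stated power at all.

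**Working it through.** **1. The plan's own figure.** For two means, n = 2·SD²·(z₀.₉₇₅ + z₀.₉₀)² / δ². The inputs are δ = 3, two-sided 0.05, power 0.90 and n = 45 (Sample size). No SD is given, so 45 cannot be reproduced, but it can be solved backwards:

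SD = 3 × √(45/2) / (1.960 + 1.282) = 3 × 4.743 / 3.242 ≈ 4.39 by the normal approximation, or 4.34 by the two-sample t-test.

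The loss step does reproduce: 45 / 0.85 = 52.9, rounded up to 53, and 53 × 4 = 212. So 45 fits one two-group MMSE comparison at an undivided 0.05 if the SD is about 4.34 to 4.39.

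**2. Chance of at least one false positive if any primary result counts at 0.05.** Four equal arms were simulated with no true effect and outcome correlation from 0 to 0.7 (an assumption; none is stated).

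| Reading | Tests | Correlation 0 | Correlation 0.7 |
|---|---|---|---|
| 3 outcomes, each arm against control | 9 | 33% | 26% |
| 3 outcomes, all pairs | 18 | 49% | 39% |
| 2 outcomes (handgrip not primary, as in the abstract), each arm against control | 6 | 23% | 20% |
| 3 outcomes, one four-group omnibus test each | 3 | 14% | 11% |
| MMSE alone, each arm against control | 3 | 12.5% | 12.5% |

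The zero-correlation column can be checked by hand. MMSE against three arms sharing a control gives 0.125, so three independent outcomes give 1 − 0.875³ = 0.33. Six MMSE pairs give 0.203, so three outcomes give 1 − 0.797³ = 0.49. Three omnibus tests give 1 − 0.95³ = 0.14.

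**3. Power for one MMSE contrast if the error is controlled.** Power ≈ Φ(δ / (SD·√(2/n)) − z). With SD 4.39 and n = 45 the first term is 3 / (4.39 × 0.2108) = 3.242.

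- At 0.05/3: Φ(3.242 − 2.394) = Φ(0.848) ≈ 0.80.
- At 0.05/9: Φ(3.242 − 2.773) = Φ(0.469) ≈ 0.68.

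The t-test with SD 4.34 gives 0.80 and 0.67, and 0.81 for Dunnett with three contrasts (level 0.0189 per contrast). The difference detectable with 90% power rises from 3.0 points to 3.4 (0.05/3) or 3.8 (0.05/9).

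**4. Effect of baseline adjustment.** ANCOVA on baseline MMSE with correlation r reduces the SD to SD·√(1 − r²). If 4.34 is a raw SD, r = 0.5 gives 4.34 × √0.75 = 3.76. The t-test power at 45 per group is then:

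| Assumed raw SD | r | 0.05 | 0.05/3 | 0.05/9 |
|---|---|---|---|---|
| 4.34 | 0 | 0.90 | 0.80 | 0.67 |
| 4.34 | 0.5 | 0.96 | 0.91 | 0.82 |
| 4.34 | 0.7 | 0.995 | 0.98 | 0.96 |
| 5 | 0 | 0.80 | 0.66 | 0.50 |
| 5 | 0.5 | 0.90 | 0.80 | 0.67 |

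If 4.34 is already an adjusted SD, the r = 0 row applies.

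**5. What each success rule would imply.**

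- *Any win at 0.05:* error as in step 2. The single MMSE contrast keeps its 0.90.
- *One named contrast must win on all three outcomes:* error at most 5%. With 90% power for each outcome, joint power is 73% to 83% for outcome correlation 0 to 0.8.
- *Fixed order starting with one named MMSE contrast:* 5% and 0.90 both hold for that contrast.

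**The case against.** A reader might infer that the trial has neither a 5% error rate nor 90% power. The article does not support that. The inflated error arises only without a correction, and then the MMSE contrast keeps its 0.90. The reduced power arises only with a correction, and then the error is held at 5%. No single analysis has both faults, and under a fixed-order rule starting with one MMSE contrast neither appears.

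A second tempting reading is that the protocol orders nine or more tests at 0.05 each. The sentence on the level says neither that it applies per test nor that nothing will be adjusted, and no contrasts are listed. A multiplicity procedure is also commonly left to a statistical analysis plan, and one may exist. This stands as regards the choice of procedure. It does not rescue the sample size, which is fixed in the article at an undivided level for one comparison, nor the disagreement between abstract and methods over which outcomes are primary.

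Third, the lower power figures rest on a back-solved SD and a t-test, whereas the plan is ANCOVA or mixed models. This also stands: a flat statement that true power is 0.80 or 0.67 would be unsupported. Equally, the recovery to 0.91 or 0.82 needs a baseline correlation that the article does not give.

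Finally, making the physical outcomes wait for a significant MMSE result is debatable when one arm is exercise alone, since a failed cognitive test could block a physical claim.

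**Conclusion.** The point holds in a limited form. As written, the error rate for a primary claim is not controlled. If any primary result counts, it is about 11% to 49% over the readings tabulated, and 26% to 33% for the most natural one, nine comparisons with control. These figures assume outcome correlation between 0 and 0.7.

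The 0.90 power is supported only for one unadjusted MMSE comparison. Under control at 45 per group it is about 0.80 to 0.81 for three control contrasts and about 0.67 at 0.05/9, if the SD is 4.34 and there is no baseline adjustment. It is about 0.91 and 0.82 if that SD is raw and the baseline correlation is 0.5. Confidence is high that the success rule is undefined and that the sample size makes no allowance for multiplicity. It is only moderate for any particular adjusted power, because neither the SD nor the correlation is stated.

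**What to change.** Before any unblinded analysis:

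1. Reconcile the primary outcomes between the abstract and Primary outcome measures.
2. State the three contrasts with control as the primary family.
3. Control the family-wise error at 0.05 in one of two ways. Either keep the several primary outcomes and apply Holm over all outcome-by-arm tests, or make MMSE the single primary outcome and apply Dunnett or Holm to its three contrasts. The first keeps a primary physical claim open to the exercise arm. The second matches the outcome the trial was sized on, but demotes listed primary outcomes and should be recorded as an amendment.
4. Restate the power at the adjusted level, with the SD, the assumed baseline correlation and a range, and say that no power is given for handgrip or HABAM if they remain primary.

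No more patients need be enrolled. The price is a documented change of plan, a stricter threshold for each test and probably a less favourable stated power.
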